### dGEMRIC

Following MRI acquisition, dGEMRIC analysis will be carried out using a methodology closely based on that validated in previously published studies [47]. Acetabular and femoral head cartilage ROIs will be defined for three mid-sagittal plane slices at the chondrolabral transitional zone, reaching approximately 3 to 6 mm toward the acetabular fossa in each hip. Accurate positioning of the mid-sagittal plane was ensured using a three-dimensional view of the hip volume in Osirix (version 8, Geneva, Switzerland [48]; see Fig. 2). This cartilage subregion has been chosen for analysis due to its relevance in the pathogenesis of FAI [4, 49]. Care will be taken to define ROIs including only acetabular and femoral head cartilage separately, while excluding labrum and bone. The mean change in T_1_ values between baseline and 12 months for these ROIs will be reported.

**Fig. 2 Fig2:**
[figure not shown]
Selection of mid-sagittal plane for dGEMRIC analysis. Selection of the mid-sagittal plane using OsiriX. dGEMRIC analysis will be performed on the three mid-sagittal slices

We will also calculate z-scores for the acetabular and femoral cartilage ROIs at the chondrolabral junction, using the standardised dGEMRIC method proposed by Lattanzi et al. [31, 32]. Standardised dGEMRIC uses the healthy central femoral head cartilage as an internal control to which other cartilage ROIs can be compared, by transforming the T_1_ values (x) to standard scores (z) using z = (x - μ) / σ, where μ and σ are the mean and standard deviation, respectively, of T1 values within the central femoral head cartilage ROI. Standardised dGEMRIC enables better comparison of local cartilage damage between different individuals as it removes the effect of individual-level factors affecting T_1_ values such as age, sex, BMI, and differences in gadolinium diffusion and transport rates through cartilage [31]. Standardised dGEMRIC z-scores will be reported at baseline and 12 months for acetabular and femoral ROIs at the chondrolabral junction, with a central femoral cartilage ROI to be used as an internal control. By measuring and reporting the change in standardised dGEMRIC scores between baseline and 12 months, we will mitigate the effect that surgical trauma has been posited to have in reducing cartilage T_1_ values globally for a period of time following surgery [50, 51]. Change in standardised dGEMRIC z-scores between baseline and 12 months may provide a more accurate reflection of local changes in cartilage health at the FAI-relevant chondrolabral junction.

### Plain radiograph

All participants will have plain X-rays at baseline and 12 months. At baseline, a supine anterior-posterior (AP) pelvis, 45-degree modified Dunn view and false profile view X-ray will be acquired. At 12 months, a supine AP pelvis and modified Dunn view will be acquired. A detailed protocol will be provided to radiographers to ensure consistent patient and X-ray beam positioning between cases [52]. A comprehensive set of radiographic measurements applicable to FAI pathoanatomy will be measured using Hip2Norm software, which has been validated for this purpose [53]. These measures include: pelvic orientation, acetabular anteversion, acetabular depth, acetabular inclination, femoral head coverage, femoral head sphericity, joint space width, and joint congruity. These data will be reported at baseline and 12 months, enabling characterisation of the effects of surgery on the pathoanatomy of FAI.

### Motion analysis EMG data collection

Participants enrolled in Melbourne will undergo motion analysis during walking, squatting, and jogging at baseline and 12 months. A 12-camera Vicon motion capture system (Vicon, Oxford Metrics, UK) will be used to acquire three-dimensional motion data of participants wearing a full-body marker set with modified lower limb 10-marker clusters at 120 Hz) [54]. Ground reaction forces will be acquired using two AMTI (Advanced Mechanical Technology Institute, Massachusetts, USA) force plates sampling at 1200 Hz. electromyograms will be acquired with a Noraxon DTS 2400 wireless telemetry system from 14 muscles of the study limb, sampling at 1200 Hz. According to surface electromyography for the non-invasive assessment of muscles (SENIAM) guidelines [55], surface electrodes will be placed on the soleus, medial and lateral gastroncnemii, hamstrings, vasti, rectus femoris, tibialis anterior, peroneals, adductors, tensor fasciae latae, gluteus maximus, and gluteus medius. Biomechanical outcome parameters will include tri-planar kinematics and kinetics of the lower-limb segments and joints, and relevant pelvis and trunk kinematics.

Calibrated EMG-informed Neuromusculoskeletal (CEINMS) [56] and Finite Element Method (FEM) models will be used to calculate stress and strain fields, as well as strain energy density, of the acetabular and femoral cartilages to determine cartilage loading stimulus at baseline and 12 months [57]. The MRI and gait analysis data will be employed to create patient-specific lower-limb rigid body musculoskeletal models and FEM hip meshes using the Musculoskeletal Atlas Project (MAP) software [58]. The EMG-informed muscle-tendon and joint contact forces will be determined using CEINMS and then applied as force-boundary conditions to a FEM model of the hip. We will then resolve the stress and strain distributions in the hip bones and cartilages using FEBio (febio.org), which is validated, Open-source FEM software specifically designed for biomechanics applications [59].

### Hip muscle strength assessment

Participants who attend the gait laboratory for motion analysis will have their hip muscle strength assessed at baseline and 12 months. A digital dynamometer force gauge (Sparker Instruments, China) will be used to assess peak isometric hip flexion, extension, adduction, and abduction strengths. For each hip strength assessment, participants will stand upright within a testing frame with the force transducer secured via a perpendicular strap around the lower thigh to the frame (see Fig. 3). The distance from the greater trochanter to the force transducer thigh attachment will be recorded as the lever arm distance in metres (m). For the study leg, participants will perform two submaximal efforts for familiarisation. Participants will then perform two maximal efforts and will be encouraged to pull as hard they can for 3–5 s with a short rest period between each of the two maximal trials. From the two maximal trials, the peak torque in Newton metres (Nm) will be determined and normalised to body mass (Nm/kg).

**Fig. 3 Fig3:**
[figure not shown]
Hip muscle strength assessment. For hip muscle group strength assessment, participants are instructed to stand upright, look straight ahead and use the rail for light finger-tip support. Following familiarisation participants receive strong verbal encouragement to pull as hard as possible. Two maximal efforts for each hip muscle group are recorded

### Patient reported outcomes

Patient reported outcomes will be collected at baseline, 6 months, and 12 months, as described in Table 1. The modified World Health Organisation Health and Work Performance Questionnaire (WHO HPQ) [38] will be utilised to assess cost-effectiveness of the interventions. Changes in participant symptoms and quality of life will be assessed using the iHOT-33 [39], the HOOS [40–42], EQ-5D [43] and the SF-12 [44]. A Global Improvement Scale (GIS) will be used to determine patient perceived overall improvement at 6 months and 12 months following baseline. Patient satisfaction will be measured on a five-point Likert scale after 12 months, in response to the questions, *“Overall, how satisfied are you with the treatment you received?”* and *“Overall, how satisfied are you with the results of your treatment?”.*

### Need for further procedures

The need for any further treatments will be recorded for participants in both arms of the study. Further treatments may include but are not limited to hip arthroscopy, open hip preservation surgery, hip replacement, or additional non-protocol physiotherapy. The need for further procedures will be ascertained by questionnaire at two years and three years.

### Adverse events

The number and type of adverse events will be recorded for all participants up to 12 months. Adverse events (AE) are defined as any untoward medical occurrence in a clinical trial patient and which do not necessarily have a causal relationship with the treatment. All AEs will be listed on the appropriate Case Report Form for routine return to the researchers. Serious adverse events (SAE) are defined as any untoward and unexpected medical occurrence that: results in death; is life-threatening; requires hospitalisation or prolongation of existing inpatients hospitalisation; results in persistent or significant disability or incapacity; is a congenital anomaly or birth defect; or any other important medical condition which, although not included in the above, may require medical or surgical intervention to prevent one of the outcomes listed. All SAEs will be reported to the ethics committee within 72 h of the investigators becoming aware of them. All participants experiencing SAEs will be followed-up as per protocol until the end of the trial.

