#### Secondary objectives

Compare 12-month change in hip cartilage health between treatment groups, as demonstrated by changes in the dGEMRIC scores of separate acetabular and femoral head cartilage ROIs at the chondrolabral transitional zone.Compare 12-month change in hip MRI and plain X-ray features between treatment groups, using the Hip Osteoarthritis MRI Scoring System (HOAMS) and Hip2Norm software, respectively.Compare 12-month change in hip joint three-dimensional stresses and strains during walking and various functional tasks between treatment groups.Determine if changes in hip joint structure after 12 months are related to symptomatic improvements.Compare 12-month change in hip muscle activation patterns and co-contraction patterns between treatment groups.Compare 12-month change in hip joint motion and moments in gait between treatment groups.Compare 12-month change in hip isometric muscle strength between treatment groups.Compare 12-month change in hip joint contact forces between treatment groups.

The objectives of the UK FASHIoN trial [25] are secondary objectives of our trial, and include:Compare changes in patient-reported hip-specific quality of life after 12 months, as measured by the international Hip Outcome Tool-33 (iHOT-33).Compare changes between treatment groups in general health status and health-related quality of life after 12 months, as measured by the Short Form-12 (SF-12).Compare differences between treatment groups in patient satisfaction with treatment and outcome after 12 months.Compare differences between treatment groups in the number and severity of adverse events after treatment after 12 months.Compare differences between treatment groups in the need for further surgical procedures up to three years.Compare the cost-effectiveness of hip arthroscopy for FAI with non-surgical care, within the trial, and estimated for a patient’s lifetime.Measure fidelity of delivery of interventions.

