Other secondary outcomes will include hip joint structural change between baseline and 12 months as demonstrated by the semi-quantitative whole Hip OA MRI Score (HOAMS), and by plain radiographic and MRI measures of alpha angle, acetabular depth, femoral and acetabular version; change between baseline and 12 months in hip joint biomechanics during gait and functional tasks as measured by external hip joint motion and moments, muscle activation and co-contraction patterns, net hip joint contact forces in localised regions of cartilage, and regional cartilage stresses and strains; cost-effectiveness of the interventions as measured by the modified World Health Organisation Health and Work Performance Questionnaire (WHO HPQ) [38]; changes in participant symptoms and quality of life as measured by the international Hip Outcome Tool-33 (iHOT-33) [39], the Hip disability and Osteoarthritis Outcome Score (HOOS) [40–42], EQ-5D [43], and the 12-Item Short Form Health Survey (SF-12) [44]; patient perceived overall improvement following intervention measured using a Global Improvement Scale (GIS); and patient satisfaction with care and treatment results measured on a five-point Likert scale. Procedures for measurement and analysis of each of the secondary outcomes is described in greater detail below. The table of data collection and time points (see Table 1) summarises the timeline for each of the study procedures.

**Table 1 Tab1:** Table of data collection and time points

Time points:	Baseline	6 months	12 months	24 & 36 months
Data collection:	Demographic information Physical activity (modified UCLA Activity Scale) MRI scan dGEMRIC scan Plain radiography 3D gait analysis EMG-informed NMS and FEM models iHOT-33 HOOS SF-12 EQ-5D WHO HPQ (modified)	iHOT-33 HOOS GIS SF-12 EQ-5D WHO HPQ (modified)	MRI scan dGEMRIC scan Plain radiography 3D gait analysis EMG-informed NMS and FEM models, iHOT-33 HOOS GIS SF-12 EQ-5D Patient satisfaction Resource utilization Adverse events WHO HPQ (modified)	Further procedures questionnaire

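### The SAE definition requires an event to be unexpected, so serious but recognised complications fall outside the SAE count and the 72 h ethics-committee report

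*Protocol article*

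**What the plan says.** Two definitions stand side by side in the Adverse events section of the protocol article. The broad one is: "Adverse events (AE) are defined as any untoward medical occurrence in a clinical trial patient", with no causal link to treatment required. The narrow one is: "Serious adverse events (SAE) are defined as any untoward and unexpected medical occurrence that: results in death; is life-threatening; requires hospitalisation". The list then continues with a lengthened inpatient stay, lasting disability, congenital anomaly, and other important conditions that may need intervention to avert one of these outcomes.

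The two classes are handled differently. For all events: "The number and type of adverse events will be recorded for all participants up to 12 months", and "All AEs will be listed on the appropriate Case Report Form for routine return to the researchers". For serious ones: "All SAEs will be reported to the ethics committee within 72 h of the investigators becoming aware of them". Participants with an SAE also carry an explicit follow-up commitment to the end of the trial.

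One of the Secondary objectives is: "Compare differences between treatment groups in the number and severity of adverse events after treatment after 12 months". The Statistical analysis section compares adverse events, intervention complications and further procedures between arms by chi-squared or Fisher's exact test. Data safety and monitoring gives the independent board oversight of adverse events, SAEs and treatment side effects.

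**The concern.** Seriousness describes what happened to the participant. Expectedness describes whether the event was foreseeable for the treatment given. Both matter, but they answer different questions and are normally recorded as separate attributes. Here they are joined by *and*, so an event must pass both tests to be called serious.

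Two things are at stake. The first is reporting: the 72 h rule applies to SAEs only, so a serious event judged foreseeable goes through routine return of the case report form. The second is the harm comparison. The trial promises to compare the severity of adverse events as well as their number, and the SAE label is the only grading of events that the article defines. If that label omits serious events because they were foreseeable, a table of SAEs by arm does not show how many participants in each arm had a serious event. In a comparison of elective surgery with physiotherapy-led care, readers will look at that table closely.

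**Working it through.** No arithmetic applies: the point turns on a definition and the article gives no event rates. The check is to apply the definitions as written to each kind of event and follow it through the sections that use the labels.

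| Event | AE? | SAE as written? | On the case report form? | 72 h ethics report? | In the between-arm AE and complication comparisons? | Within the board's remit? |
|---|---|---|---|---|---|---|
| Not serious, expected or not | yes | no | yes | no | yes | yes |
| Serious and unexpected | yes | yes | yes | yes | yes | yes |
| Serious and expected | yes | **no** | yes | **no** | yes | yes, but not as an SAE |

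The defect is confined to the third row.

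1. **Is the exclusion corrected elsewhere?** No. The Statistical analysis and Data safety and monitoring sections use the labels without redefining them.
2. **Is *unexpected* needed to keep the planned operation out of the SAE list?** No. Admission for the allocated surgery is not untoward, so the first condition already excludes it.
3. **Does another grading make up the loss?** Not in the article. The objective speaks of number and severity; the recording rule names number and type. The planned tests treat adverse events and complications as dichotomous outcomes, so a complication that leads to readmission counts the same as a minor one.
4. **Would the exclusion fall equally on both arms?** Probably not. Surgery involves general anaesthesia, bony resection, anchors and a hospital stay, and the criterion of a prolonged stay bears chiefly on that arm. Physiotherapy-led care is exercise, education and pain-relief advice, but may include referral for an intra-articular steroid injection, so it is not free of foreseeable events. Without rates or a list of expected events, the direction is an inference and the size is unknown.
5. **Is the filter applied uniformly?** The article does not say who judges expectedness or against what list. With eight surgeons, eleven named hospital sites and unblinded treating clinicians, the same event could be classified differently from place to place.

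**The case against.** The strongest reply is that nothing disappears. Every untoward occurrence is an AE, all AEs go on the case report form, and a readmission after arthroscopy would enter the comparison under at least one of two headings, adverse events or intervention complications. The board oversees AEs and treatment side effects as well as SAEs. All of this stands. A reader might infer that the trial under-reports harm as a whole, or that safety oversight is delayed throughout; the document supports neither. What is narrowed is the SAE label and the notification of the ethics committee.

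A second reply is that the article never specifies a between-arm test of SAEs, and that severity and seriousness are themselves different concepts. This also stands, and it makes the effect on the harm comparison conditional: it affects any SAE tabulation that is produced, not the specified comparisons of adverse events and complications. It does not remove the problem, because no other grading is defined through which the severity objective could be met.

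A reader might go further and conclude that the rule favours surgery by some stated amount. There are no figures here from which to derive one.

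A reader might also take Table 1, whose 12-month column includes "Patient satisfaction Resource utilization Adverse events WHO HPQ (modified" while its 6-month column has no adverse event entry, to mean that events are gathered once by year-long recall. The text does not support that: it describes recording on a case report form up to 12 months, and the table entry may simply mark the end of that window.

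**Conclusion.** The concern holds in a limited form. As written, serious events from recognised complications are AEs but not SAEs. They therefore miss the SAE count, the 72 h report to the ethics committee and the follow-up commitment attached to SAEs. They remain recorded, compared as adverse events or complications, and open to the monitoring board, although its SAE listing would be incomplete.

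The size cannot be stated. A greater loss in the surgical arm is plausible from the nature of the interventions, but it is unconfirmed. The conclusion assumes that sites apply the definition literally; sites that ignore *unexpected* would lose fewer events but would then classify differently from sites that follow it. The primary outcome is not touched.

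This should be fixed. It is an error in a stated rule rather than a detail that a condensed article leaves to the full protocol, but it does not threaten the main result.

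**What to change.** - Delete the requirement that an SAE be unexpected, so that seriousness rests on the listed outcome criteria alone. If the intention was to exclude the planned surgical admission, say so in its own sentence.
- Record expectedness and relatedness as separate attributes of each SAE.
- Tabulate all serious events by arm, whether or not they were expected.
- State separately which serious events need expedited reporting. If the sponsor wants to limit the 72 h report, that limit belongs in the reporting rule and not in the definition.

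The cost is a wording amendment and somewhat more SAE reports. It is best done while events are still being classified, because reclassification is hardest after close-out. Serious but expected events already listed only as AEs would need to be identified from the case report forms and relabelled.

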### Statistical analysis

#### Descriptive analysis

Data will be checked for outliers and missing values, and validated using the defined score ranges for all outcome measures. Standard statistical summaries (medians, ranges, means, standard deviations; dependent on the distribution of the outcome) will be presented for all outcome measures. Scatter plots depicting the relationship between relevant outcomes will be presented with corresponding correlation coefficients. Counts with percentages will be presented for categorical variables. Baseline data will be summarized to check comparability between treatment arms, and to highlight any systematic differences between those individuals in the study, those ineligible, and those eligible but withholding consent. Comparisons in baseline characteristics for categorical variables will be based on χ^2^ test or Fisher’s exact test, if expected cell counts are small. For continuous variables two-group comparisons will be performed using t-tests or the Wilcoxon rank-sum test for non-normal data. Data may not be available due to voluntary withdrawal of patients, lack of completion of individual data items or general loss to follow-up. Where possible the reasons for missing data will be ascertained and reported. If judged appropriate, missing data will be imputed using a multiple imputation strategy. Any imputation methods used for scores and other derived variables will be carefully considered and justified, and analysis of imputed datasets used to assess the sensitivity of the analysis to the missing data.

The primary analysis will be of the change in the dGEMRIC index score for a combined acetabular and femoral head cartilage ROI from baseline to 12 months, with the difference in mean change between the two treatment groups presented with a 95% confidence interval and compared using an independent samples t-test. This strategy will also be applied for the standardised dGEMRIC z-scores. Change in scores for the dGEMRIC data will be assumed to be normally distributed; possibly after appropriate variance-stabilising transformation of the individual time-point scores. Analysis including adjustment for baseline dGEMRIC index score and relevant baseline characteristics will be performed using Analysis of Covariance with the change from baseline modelled as the dependent variable. This strategy will also be applied for the dGEMRIC index score of the separate acetabular and femoral head cartilage ROIs and the standardized dGEMRIC z-scores.

The above strategy will also be performed for analysis of other approximately normally distributed secondary outcome measures including those related to plain radiography, MRI, muscle strength, full 3D gait analyses, EMG-informed NMS and FEM models, and the patient reported outcomes (iHOT-33, HOOS, EQ-5D and SF-12). Differences in dichotomous outcome variables such as adverse events, complications related to the trial interventions and the need for further procedures will be compared between groups using chi-squared tests (or Fisher’s exact test). The temporal patterns of complications and the need for further procedures will be presented graphically. If there are sufficient events cumulative incidence curves of the time to first procedure (any or a specific type) will be plotted by treatment group calculated using the Kaplan-Meier method. Ordinal scores for patient satisfaction will be compared between intervention groups using proportional odds logistic regression analysis with the proportional odds assumption checked. Although our inferences will be drawn from the intention-to-treat analysis, we will perform per protocol analyses to place these in context. We plan to perform exploratory subgroup analyses by FAI type and by whether referral to the study was via the private or public healthcare systems. We do not anticipate that crossovers will be a major issue for this study. We, therefore, expect the main analyses to provide definitive results. If participant adherence to or completion of the PHT proves to be more problematic than expected, we will augment the planned analysis with a complier average causal effect (CACE) analysis.

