## Methods/design

### Trial design

This trial will be conducted in compliance with the Australian National Health and Medical Research Council (NHMRC) National Statement on Ethical Conduct in Human Research (2007), the Note for Guidance on Good Clinical Practice (CPMP/ICH-135/95), and the conditions of the ethics approval granted by St Vincent’s Hospital Human Research Ethics Committee (HREC/14/SVH/343). Results for this trial will be reported in accordance with the CONSORT statement.

The protocol for Australian FASHIoN is similar to that for the parallel UK FASHIoN trial [25], and benefits from the feasibility study performed for the UK trial [26, 27] and from collaboration between the Australian and UK research groups. Inclusion and exclusion criteria, and intervention specifications are identical. Patient-reported outcomes and timing of those outcome assessments are the same. The key differences are the mechanistic structural and biomechanical outcomes investigated in the Australian FASHIoN trial.

The Australian FASHIoN trial is a pragmatic, assessor- and statistician-blinded, two-arm superiority RCT with 1:1 allocation ratio. 140 participants will be recruited from the private and/or public clinics of eight orthopaedic surgeons, spread across three regions in Australia. Recruitment and/or arthroscopic surgery will be carried out at the following hospital sites; in New South Wales (NSW): Mater Hospital, Norwest Hospital, Sydney Adventist Hospital, St George Private Hospital, St Luke’s Hospital, Sutherland Hospital; in Victoria (VIC): Maroondah Hospital, St Vincent’s Private Hospital (East Melbourne), Western Health; and in the Australian Capital Territory (ACT): Canberra Hospital, Calvary Hospital. The PHT program will be administered at various private physiotherapy clinics located throughout NSW, VIC and ACT.

PHT will commence after treatment allocation and continue for a maximum of six months, with six compulsory physiotherapy sessions within the first 12 weeks and up to ten sessions over the first six months if needed by the participant. Arthroscopic hip surgery will occur as soon as practicable and no more than 18 weeks after treatment allocation. Post-operative rehabilitation will not be standardised, and will occur as per each participating orthopaedic surgeon’s usual rehabilitation protocol. The primary outcome will be measured 12 months post-randomisation. For further details, see Trial Design flow chart (see Fig. 1).

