### Randomisation

Randomisation to either arthroscopic hip surgery or non-surgical physiotherapy-led care will occur in a 1:1 ratio using a computer-generated minimisation sequence (adaptive stratified sampling) with study site and type of FAI (cam, pincer or mixed FAI) as factors. Allocation concealment will be preserved by having randomisation codes held by an external biostatistician. At randomisation, participants will be given a study ID that will be used on all trial documentation.

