### MRI

All participants will undergo an MRI scan at baseline and 12 months, performed on one of three 3 T MRI scanners using a phased array coil on a Siemens Prisma (Melbourne), Siemens Skyra (Sydney), or Phillips Ingenia (Canberra). Participants will be scanned on the same scanner at baseline and 12 months. Participants will receive an intravenous injection of the contrast agent; 0.2 mmol/kg bodyweight of Dotarem (Gd-DOTA; Guerbet, Cedex, France) or Magnevist (Gd-DTPA; Berlex Labs, Wayne, NJ). Following injection of contrast agent, participants will walk for 15 min, after which MRI scanning will occur.

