### Sample size

Sample size calculations for the primary outcome are based on statistical power of 90%, and two-sided significance of 5% significance level. With a sample size of 54 patients in each group, we expect to detect a difference of at least 50 ms between two study groups at 12 months based on a standard deviation (SD) of 80 ms for the dGEMRIC index [65, 66]. 50 ms was chosen as clinically significant based upon increased risk of subsequent total hip replacement [67].

Previous research identified an R^2^ ≈ 0.2–0.3 between indirect external measures of hip joint loading and hip neck bone density in people with hip OA, when two covariates (weight and height) were included, indicating a moderate relationship between biomechanical and structural measures. We expect higher R^2^ values, given that we have direct estimates of cartilage stress and strain. Being conservative, however, in order to achieve an R^2^ > 0.2 between cartilage loading stimulus and dGEMRIC scores (with three covariates), a power of 90%, and a two-sided significance level of 5% we require a total of 56 patients at each site. We will, therefore, aim to recruit a total of 140 participants for the study to allow for a drop-out rate of 20%, including 5% cross over to the surgical group.

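### The primary analysis is an unadjusted t-test on change; promoting the planned ANCOVA, with the minimisation factors named, would give a more precise headline result at no data cost

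*Protocol article*

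**What the plan says.** All places are in the protocol article.

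- **Primary analysis** (Statistical analysis, under Descriptive analysis). The outcome is the 12-month change in the combined-ROI dGEMRIC index. What is planned for it is "the difference in mean change between the two treatment groups presented with a 95% confidence interval and compared using an independent samples t-test". No covariate enters.
- **Adjusted analysis** (same section). "Analysis including adjustment for baseline dGEMRIC index score and relevant baseline characteristics will be performed using Analysis of Covariance"; the dependent variable is change. It is not called primary, and its further covariates are not named. The same approach is carried to the separate ROIs, the z-scores and the other approximately normal secondary outcomes.
- **Allocation** (Randomisation). A "computer-generated minimisation sequence (adaptive stratified sampling) with study site and type of FAI (cam, pincer or mixed FAI) as factors".
- **Imaging** (MRI). Scans are "performed on one of three 3 T MRI scanners", and each participant uses the same scanner at both visits.
- **Sample size**. The basis is "statistical power of 90%, and two-sided significance of 5% significance level", a 50 ms difference at 12 months and an SD of 80 ms for the dGEMRIC index. The result is stated as "With a sample size of 54 patients in each group". The article does not say whether 80 ms is the SD at one visit or the SD of change.

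**The concern.** Baseline dGEMRIC is measured in everyone, and allocation is balanced on two factors thought important enough to control. The headline test makes limited use of the first and none of the second. A change score subtracts baseline with the slope fixed at 1, whereas ANCOVA estimates the slope. When the true slope is below 1, the change score adds noise and carries part of any chance baseline imbalance into that trial's estimate.

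Separately, when allocation is balanced on factors that predict the outcome and the analysis leaves them out, the reported standard error is larger than the true one.

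At stake are the width of the headline confidence interval and, on one reading of the planning SD, whether the stated power is reached.

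**Working it through.** **1. The plan's own figure.** Inputs from Sample size: difference 50 ms, SD 80 ms, two-sided 5%, power 90%.

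n per arm = 2 × (1.96 + 1.2816)² × 80² / 50² = 53.8, so 54.

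The stated 54 is reproduced; power is 90.1% by the normal formula and 89.6% by the noncentral t. Allowing for 20% loss, 108 / 0.8 = 135, which is within the 140 planned.

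**2. Change score against ANCOVA in general.** Let s0 and s1 be the SDs at baseline and 12 months, and ρ their correlation.

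- Variance of change: s0² + s1² − 2ρ·s0·s1
- ANCOVA residual variance: s1²(1 − ρ²)
- Difference: (s0 − ρ·s1)², which is never negative

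So, in large samples, ANCOVA is never less precise. The two are equal only if the slope ρ·s1/s0 is 1. With s0 = s1, the ratio of standard errors is √(2/(1 + ρ)).

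**3. If 80 ms is a single-visit SD, equal at both visits.** ρ is assumed. SD of change = 80√(2(1 − ρ)); ANCOVA SD = 80√(1 − ρ²). At 54 per arm, 95% CI half-width = 1.96 × SD × √(2/54) and power = Φ(50/(SD√(2/54)) − 1.96). Each cell gives t-test / ANCOVA.

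| ρ | SD, ms | SE ratio | CI half-width, ms | Power | n per arm for 90% |
|---|---|---|---|---|---|
| 0.3 | 94.7 / 76.3 | 1.24 | 35.7 / 28.8 | 78.4% / 92.6% | 76 / 49 |
| 0.5 | 80.0 / 69.3 | 1.15 | 30.2 / 26.1 | 90.1% / 96.3% | 54 / 41 |
| 0.7 | 62.0 / 57.1 | 1.08 | 23.4 / 21.6 | 98.7% / 99.5% | 33 / 28 |

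The t-test reaches 90% only from ρ = 0.5 upward, where the SD of change is 80 ms or less. ANCOVA already has 90.1% at ρ = 0.

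**4. If 80 ms is the SD of change.** The t-test has its 90% by construction. The ANCOVA SD is 80√((1 + ρ)/2) = 64.5, 69.3 and 73.8 ms at ρ = 0.3, 0.5 and 0.7. Power is then 98.1%, 96.3% and 94.1%, and 35, 41 or 46 per arm would give 90%.

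**5. Minimisation factors.** This was simulated with 108 analysed, SD of change 80 ms and 4,000 trials per setting. Three sites (45/40/15%), three FAI types (70/10/20%) and a biased-coin probability of 0.8 were assumed. The t-test's reported SE is 80√(2/54) = 15.4 ms throughout.

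| Share of change variance explained by site and FAI type | True SE, ms | Type I error of t-test |
|---|---|---|
| 0% | 15.4 | 5.4% |
| 10% | 14.5 | 3.4% |
| 20% | 14.0 | 3.1% |
| 30% | 13.2 | 2.4% |

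Simulation error is about 0.3 percentage points at 5% (√(0.05 × 0.95/4000)), so the 5.4% is compatible with 5%. At 20% explained, the reported SE is 15.4/14.0 = 1.10 times the true one. With both factors in the model, type I error was about 4.5% to 5.2%. When the factors explained nothing, including them raised the average reported SE only from 15.36 to 15.40 ms.

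**The case against.** The best defence is that the t-test is a legitimate choice: simple, valid, unbiased over randomisation and, at worst, conservative. The ANCOVA is already planned, and naming its covariates is ordinary analysis-plan work. The open term for baseline characteristics may well include site and FAI type. The size of the loss rests on a correlation that the article does not give; at 0.7 the power difference is trivial. All of this stands. It does not reach the point that the article itself fixes the less precise of its two analyses as primary.

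A reader might infer more than the text supports:

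- **That the plan leaves open which analysis decides.** It does not; the t-test is presented as the primary analysis.
- **That baseline is ignored.** The change score uses it, with slope 1. What is missing is adjustment.
- **That the confidence interval is necessarily too wide for the allocation, with type I error below 5%.** This holds only if site or FAI type predicts change. If they explain none of it, there is no effect.
- **That three scanners make site strongly prognostic.** Each participant stays on one scanner, so additive offsets cancel in the change. Site may predict the level of dGEMRIC and hardly predict its change.
- **That the trial is underpowered.** This needs both a single-visit reading of 80 ms and a correlation below 0.5. The article establishes neither.
- **That covariates will be picked from baseline significance tests.** Those tests are planned to check comparability, and the article does not say they will select covariates.

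**Conclusion.** The point holds as an efficiency recommendation. It does not make the primary analysis invalid or the sample size wrong. In large samples ANCOVA is never less precise than the change-score t-test. Under equal SDs the t-test's standard error is about 24%, 15% or 8% larger at assumed correlations of 0.3, 0.5 or 0.7. The power consequence runs from 78% against 93% to almost none, depending on that correlation and on what the 80 ms describes.

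The minimisation part is conditional and may be modest. Type I error would be about 3% if the factors explained 20% of the variance in change and would stay nominal if they explained none; any error is in the conservative direction. The case for changing the primary analysis does not depend on it.

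**What to change.** In the Statistical analysis section:

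1. Make the already planned ANCOVA the primary analysis. The covariates, named in advance, are treatment, baseline dGEMRIC of the same ROI, study site and FAI type. Change can stay as the dependent variable: with baseline in the model, the treatment estimate is the same as for the 12-month value.
2. Define site at the level used in the minimisation. The article lists eleven hospitals in three regions, and these give very different models with about 108 analysed. If the level is hospital, state beforehand how small sites are pooled.
3. Report the adjusted difference with its 95% confidence interval as the headline, and keep the t-test as a supportive unadjusted analysis.
4. Use the same order for the continuous secondary outcomes.

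The cost is wording only. No new data or participants are needed, and 140 need not change. The change should be made and dated before unblinded data are seen.
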